**Methods and Analysis:**

A prospective observational cohort study will be conducted with 194 nursing students. Participants will be asked to walk through a baropodometric platform before and after a 5-month clinical training session. Assessment will focus on the change in podiatric profile, namely foot posture and foot function, at 5 months, and changes in foot health at 5 months. The study will start in January 2022 and it's expected to end by June 2022.

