### Exposures, Outcomes and Confounders

The exposure under study consists of a particular environment that poses particular biomechanical risks to the foot/ankle region. According to Bernardes et al. (15), standing environments include those of prolonged standing and prolonged walking, which can be defined as spending at least 5% of occupational time standing or walking (21).

The first primary outcome of interest is related to the change in podiatric profile at 5 months and will be evaluated at month 0 and month 5, being an objective and quantitative outcome. In this case, specific foot-related variables while walking will be recorded, illustrating the actual behavior of the foot during activity. The assessment of the podiatric profile follows the important premise that the medial longitudinal arch is one of the most important and highly variable structural characteristic of the human foot (22).

The relevant variables that describe this outcome are summarized in Table 1.

**Table 1 T1:** Specific podiatric profile variables.

**Category**	**Variables**	**Definition**
**Kinematic variables**	Forefoot width/spreading	Distance, in millimeters, between two straight lines perpendicular to the Chopart joint and tangential to most medial and most lateral points of the heads of first and fifth metatarsals, respectively.
	Foot angle at contact (sagittal plane)	Dorsiflexion angle at contact, in relation to the sagittal plane.
	Foot eversion	Or pronation, is an angular movement where the foot moves away from the medial plane.
	Foot adduction	Is the angular movement were the foot moves toward the medial plane.
	Foot external rotation	Rotation of the joint away from the midline, measured as an angle.
	Ankle inversion	Angular movement toward the medial plane.
	Medial longitudinal arch (MLA)	Located between the heel proximately and the medial three metatarsophalangeal joints anteriorly. Runs through metatarsals 1-3, sesamoid bones, cuneiform bones, navicular, talus, and calcaneus bones; the plantar aponeurosis, spring ligament, talocalcaneal ligament, and deltoid ligament; the flexor *hallucis longus*, flexor *digitorum longus, abductor hallucis*, flexor *digitorum brevis*, tibialis posterior.
	Ankle plantarflexion ROM in late stance	Refers to the angular distance of the movement around the ankle joint during the late stance of gait, characterized by a single limb support, and occurring before the swing period.

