Another variable of interest to characterize the podiatric profile is plantar loading characteristics. As there is no current consensus in the literature for the definition of adequate foot segments, this study will consider the templates of similar studies, which showed good reliability for plantar forces and pressures during barefoot walking in healthy adults (23). Namely, the regions to assess and compare are: lateral heel, medial heel, midfoot, 1st metatarsophalangeal joint (1MPJ), 2nd−5th metatarsophalangeal joint (2–5MPJ), hallux and the lesser toes.

The second primary outcome concerns the change in foot health at 5 months, a subjective evaluation by the participant, and is related to observed clinical parameters, signs and symptoms, namely skin, nails, foot structure, as well as presence and location of the pain. The Portuguese adaptation of the Self-Administered Foot Health Assessment Instrument (S-FHAI), a Likert-type instrument with four dimensions, will be used. It will be applied at month 0 and month 5. The majority of observed foot disorders will be recorded as either present or absent.

The study also includes the following secondary outcomes: (i) Foot Self-Care Knowledge, which is assessed between month 0 and month 5, through a four-dimensional questionnaire, where specific interventions for the promotion and prevention of foot and ankle disorders are evaluated; and (ii) Students' perceptions about the influence of foot health in their quality of life. It is evaluated through focus groups after exposure time (month 5).

Regarding potential effect modifiers and confounders, we expect that different nursing activities and ward typology (e.g., surgical units, intensive care) might produce diverse baropodometric patterns.

The primary and secondary outcomes, respective instruments for evaluation and timeframes for assessment are summarized in Table 2.

**Table 2 T2:** Primary and secondary outcomes assessment.

			**Assessment**	**Timeframe**		
				**Month 0**	**Month 3**	**Month 5**
**Primary Outcomes**	Change in Podiatric Profile at 5 months^*^	Kinematic variables	EMED® software	x		x
		Kenetic variables		x		x
		Foot posture	MAI analysis	x		x
		Foot function	CPEI analysis	x		x
	Change in Foot Health at 5 months	Skin health	Portuguese adaptation of the self-administered foot health assessment instrument [S-FHAI; (24)].	x		x
		Nail health		x		x
		Foot structure		x		x
		Foot pain		x		x

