### Study Layout

After recruitment, at month 0 (before exposure) and month 5 (after exposure), the participants will undergo a four-phased procedure:

Preparation: the trials will be explained to the participants and consent will be retrieved; any questions will be properly addressed;Familiarization: a test procedure will be performed where participants walk freely over the platform, without recording baropodometric gait analysis (BGA), to achieve the greatest possible freedom of movement. Participants will be asked to always walk barefoot.Trials: three types of gait protocols are usually applied in this type of study (one-step, two-step and mid-gait protocol). The choice should be based on both the variable of interest and the site of the foot to be studied. According to some authors (25, 26), there are few differences between the mid-gait (the *standard* protocol) and the two-step protocol, with similar values provided by both. An important criterion is using the same protocol throughout all studies, including follow-up.In this study, we chose to use the mid-gait protocol (Figure 1), particularly because the two-step termination protocol method is usually more appropriate for collecting joint kinematic data, which is out of the scope of this study, and also because the two-step initiation and termination protocols might delay acquiring the usual walking velocity during the trial (25, 26). In this sense, subjects will walk, at a self-selected pace, along an 8.0 m walkway. An initial position will be pre-established, to allow the right foot to hit the pedography platform at the middle of the walkway, with the fourth step, also avoiding gait alterations. After striking the platform, subjects will continue walking for 4.0 m until de end of the walkway.Additionally, participants will perform three valid trials per foot, as it has been previously found to be sufficient to ensure adequate reliability of force and pressure data (27–29) and will perform at least three steps before and after the pedography platform, as stated by Cousins et al. (27), that gait protocols should ideally involve a minimum preamble of at least three steps for a representative gait pattern to be obtained.It should be noted that a valid trial of a foot scan is defined as the participant hitting with the whole foot over the platform, without gait pattern alterations. A trial will be excluded, and should therefore be repeated, if a participant: (i) targets the borders of the platform with any part of the foot; (ii) alters gait to ensure full contact of the foot; and (iii) pauses on the mat.Self-Assessment of Foot Health: at the end of the BGA, participants will be asked to answer a self-assessment instrument about their current foot health, including skin, nail and presence of pain and will participate in a focus group together with another 5–10 participants from the study to discuss the influence of foot health in quality of life.

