### Statistical Analysis

The primary outcomes and the Foot Self-Care Knowledge (secondary outcome) will be analyzed using SPSS Statistics v25, namely with descriptive statistics (average; standard deviation; medians) with an *a priori* significance value of *p* < 0.05.

After verifying the type of distribution of the sample, using the Kolmogorov-Smirnov (KS) with Liliefors correction (suitable for samples with more than 30 subjects) (30), either the independent samples *t*-test (normal distribution) or the Mann-Whitney (test non-normal distribution) will be used to compare changes in outcomes before and after the exposure.

To relate variables of interest, namely podiatric profile variables and specific foot-health parameters, a Multiple Linear Regression will be computed and multivariate analysis of variance with repeated measures to detect significant interactions between variables.

To control confounding effects, we'll perform a stratification of variables, and evaluate the exposure-outcome association, also using Mantel-Haenszel (M-H) estimator for an adjusted result. Additionally, the Analysis of Covariance (ANCOVA) will be computed to assess the effect of certain factors on the outcome variables.

The secondary outcome, related to the students' perceptions, will be analyzed using ATLAS.ti v7 software, based on the content analysis as defined by Bardin (31). The different phases of analysis are: (i) pre-analysis; (ii) exploration of the material; and (iii) treatment of results, inference and interpretation. The categorical organization of the content will be performed *a posteriori*, through the following codification steps: (i) cutting—choice of units; (ii) enumeration—choice of counting rules; and (iii) classification and aggregation of chosen categories and units.

Potential missing data will be handled using marginal mean imputation, this is, computing the mean of the missing value, *X*, using the non-missing values and use it to impute missing values of *X*.

Regarding loss to follow-up, all data belonging to participants that choose to opt-out or are lost during the study, will be erased from storage, as explained in the informed consent document.

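### The before/after comparison of the primary outcomes is planned with independent-samples tests, although the same students are measured at month 0 and month 5

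*Protocol article*

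**What the plan says.** **The test.** The Statistical Analysis section of the protocol article first checks the distribution of the sample with a Kolmogorov-Smirnov test. Depending on the result, the comparison is made with a t-test for independent samples, "or the Mann-Whitney (test non-normal distribution) will be used to compare changes in outcomes before and after the exposure".

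**The design.** The Abstract describes a single cohort: "A prospective observational cohort study will be conducted with 194 nursing students". Under Study Layout, "at month 0 (before exposure) and month 5 (after exposure), the participants will undergo a four-phased procedure". The first primary outcome is "related to the change in podiatric profile at 5 months and will be evaluated at month 0 and month 5" (Exposures, Outcomes and Confounders). The second, foot health on the S-FHAI, is applied at the same two times, as Table 2 confirms. On its recording, the same section says: "The majority of observed foot disorders will be recorded as either present or absent".

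**What else is named.** The Statistical Analysis section also lists multiple linear regression, a repeated-measures multivariate analysis of variance, the Mantel-Haenszel estimator and ANCOVA. The repeated-measures analysis is there to look for interactions between variables. Mantel-Haenszel is there to control confounding. Neither is assigned to the before/after comparison. No paired test is named.

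**The concern.** The independent-samples t-test and the Mann-Whitney test both assume two separate, unrelated samples. This study has only one set of students. Applied to a before/after comparison, these tests must treat the month 0 and month 5 values as if they came from different people. They discard the link between a student's two measurements, which is the main statistical advantage of measuring the same student twice.

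This is the only test that the article states for change in either primary outcome. If the two measurements correlate positively, as one would expect for the same student, the standard error and the p-value come out too large. A real change in foot posture, foot function or foot health could then be reported as no significant change. The Discussion already concedes that five months may be too short for important signs and symptoms to appear, so small changes are plausible, and small changes are where the loss is worst in relative terms.

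**Working it through.** **1. The article's own figure.** Participants and Recruitment Process gives a population of 300, 95% confidence, a 5% margin of error and a 50% response distribution.

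- n0 = 1.96² × 0.25 / 0.05² = 384.15
- n = 384.15 / (1 + 383.15/300) = 168.70, rounded up to 169
- 169 × 1.15 = 194.35, rounded to 194

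Both stated numbers are reproduced. They rest on the precision of one proportion. The article therefore gives no power, effect size, SD or within-student correlation for the before/after comparison, and the values used below are assumptions.

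**2. Inputs.** 169 pairs (from the article); alpha 0.05 (from the article, two-sided assumed); equal variances at the two times (assumed); rho from 0 to 0.8 (assumed); change of 0.1, 0.2 or 0.3 SD (assumed).

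**3. Standard error.** The true SE of the mean change is SD × sqrt(2(1 - rho)/n). The independent-samples test uses about SD × sqrt(2/n). The ratio is 1/sqrt(1 - rho).

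**4. True size of the nominal 5% test.** Size = 2 × (1 - Phi(1.96/sqrt(1 - rho))).

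| rho | SE overstated by | true size |
|---|---|---|
| 0 | 1.00 | 5% |
| 0.3 | 1.20 | 1.9% |
| 0.5 | 1.41 | 0.56% |
| 0.7 | 1.83 | 0.035% |
| 0.8 | 2.24 | 0.001% |

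**5. Power for a change of 0.2 SD, 169 pairs.** Let theta = 0.2/sqrt(2(1 - rho)/169). Paired power is about Phi(theta - 1.96). Power of the planned test is about Phi(theta - 1.96/sqrt(1 - rho)). For example, at rho 0.5, theta = 0.2 × 13 = 2.60. The paired test has Phi(0.64) = 74%; the planned test has Phi(2.60 - 2.77) = 43%.

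| rho | planned test | paired test |
|---|---|---|
| 0 | 45% | 45% |
| 0.3 | 44% | 59% |
| 0.5 | 43% | 74% |
| 0.7 | 41% | 92% |
| 0.8 | 39% | 98% |

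**6. Other sizes of change (planned vs paired).** For 0.1 SD: 7.1% vs 25.5% at rho 0.5, and 2.9% vs 38.9% at rho 0.7. For 0.3 SD: 87% vs 97% at rho 0.5, and 92.7% vs 99.9% at rho 0.7.

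**7. Simulation check (4,000 runs, 169 pairs, normal data, rho 0.5).** With no change, rejection rates were 0.006 (independent t), 0.007 (Mann-Whitney), 0.048 (paired t) and 0.046 (Wilcoxon signed-rank). With a 0.2 SD change they were 0.44, 0.41, 0.74 and 0.72. The Mann-Whitney branch has the same fault as the t-test branch.

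**The case against.** **Could the sentence mean something else?** It might be read as comparing change scores between subgroups, since ward typology is mentioned as a possible effect modifier. An independent-samples test would then be legitimate. But the sentence sets before against after and names no groups, and no unexposed group is described. This reading does not stand.

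**Is the dependence handled elsewhere?** A repeated-measures analysis is planned, so within-student dependence is not wholly ignored. It is assigned to interactions, however, and does not replace the stated test.

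**Is this detail left to a fuller plan?** An article may be silent on detail. Here it names a test, and the test does not match the design.

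**What stands on the other side.** Four stronger readings are tempting and should not be drawn:

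- *That most of the design's power is lost.* The article gives no effect size, correlation or power for this comparison. The loss runs from nothing at rho 0 to over 90% of the paired test's power for a small change with high rho (0.1 SD at rho 0.7: 38.9% to 2.9%). For a 0.3 SD change at rho 0.7 it is only 7%. One can get steep figures by fixing the change at whatever the paired test detects with 80% power: the planned test then has about 51%, 22% and 6% at rho 0.5, 0.7 and 0.8. But that benchmark change itself shrinks, from about 0.215 to 0.167 to 0.136 SD.
- *That the reported confidence intervals will be wrong.* The Statistical Analysis section plans means, SDs, medians and p-values. It plans no interval for the change.
- *That linear regression is wrong for present/absent outcomes.* The section says only that regression will relate podiatric variables to foot-health parameters. It does not say which is the dependent variable, and a present/absent item is a valid predictor.
- *That the S-FHAI can only be analysed as binary items.* It is described as a Likert-type instrument with four dimensions, so dimension-level scores are possible.

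**Conclusion.** The point holds: the article specifies tests for two independent samples on paired data, for both primary outcomes. With positive within-student correlation the error is conservative. It raises the risk of missing real changes rather than of false positives. The standard error is overstated by 1.20 to 2.24 times for rho from 0.3 to 0.8, and the true size falls from 5% to between 1.9% and 0.001%.

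Power is lost by an amount that depends on rho and on the size of the change. At 169 pairs and 0.2 SD it is 43% rather than 74% at rho 0.5, and 41% rather than 92% at rho 0.7, with no loss at rho 0. These figures assume equal variances, a two-sided 5% level and the stated values of rho and change, none of which the article supplies except the 5%. The mismatch between test and design depends on none of them.

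This must be corrected before analysis, because it concerns the stated test of the primary outcomes.

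**What to change.** Replace the independent-samples t-test and Mann-Whitney test in the Statistical Analysis section with:

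- a paired t-test on the within-student differences (month 5 minus month 0), or the Wilcoxon signed-rank test if those differences are clearly non-normal;
- the distribution check applied to the differences, not to the raw values;
- the mean change reported with a 95% confidence interval;
- where S-FHAI foot disorders are analysed as present/absent items, McNemar's test with the paired difference in proportions.

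The cost is one or two sentences and no new data. Each student's two records must be linked, which an outcome defined as change already requires.

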According to the defined criteria, all undergraduate nursing students at the third year will be recruited as participants. Each academic year, an average of 300 students are enrolled, and for a confidence interval of 95% and a margin of error of 5%, the sample size needed is 169 participants. Also, an a priori 0.05 significance level is defined and a response distribution of 50% is assumed. To prevent potential losses, we've added an additional 15% of the total sample size, thus aiming to recruit 194 students.

All data collection will take place inside the Nursing School, in specifically chosen places, previously tested for the study, and will be performed by two researchers, which will be different from those responsible to analyze data.

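### Most foot disorders are recorded as present or absent, but the methods named to relate and compare them suit continuous or ordered outcomes, and the regression's dependent variable is not named

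*Protocol article*

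**What the plan says.** **Scale of the outcome** (Protocol article, Exposures, Outcomes and Confounders). Foot health at month 0 and month 5 is the second primary outcome. It is measured with the Portuguese S-FHAI: "a Likert-type instrument with four dimensions, will be used". The same paragraph adds: "The majority of observed foot disorders will be recorded as either present or absent". No score is defined, and no prevalence is given for any disorder.

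**Methods** (Protocol article, Statistical Analysis).
- Relation between podiatric profile and foot health: "namely podiatric profile variables and specific foot-health parameters, a Multiple Linear Regression will be computed". The same sentence adds "multivariate analysis of variance with repeated measures to detect significant interactions between variables".
- Before/after change: independent-samples t-test or Mann-Whitney, chosen by a normality test.
- Effect of other factors: ANCOVA.
- Confounding: stratification, "also using Mantel-Haenszel (M-H) estimator for an adjusted result". This is the only categorical-data method named. It serves the exposure-outcome association, not the link between profile and foot health.

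The descriptive statistics listed are means, standard deviations and medians. No regression for a binary outcome appears.

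**The concern.** Relating the podiatric profile to signs and symptoms is a stated aim in the abstract, the introduction and the discussion. The article records most of those signs and symptoms as yes/no, yet the one regression it names assumes a continuous response with constant variance.

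This is more than detail left to a fuller document: a method is fixed, and it does not fit the recorded scale if the yes/no item is the response. At stake are fitted risks below zero and interval estimates that do not carry their stated confidence. The same mismatch touches the before/after comparison, where a yes/no item measured twice on the same student would go into a two-sample test of means or ranks.

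**Working it through.** **1. The plan's own figure.** The article states no figure for the regression, only a sample size: "for a confidence interval of 95% and a margin of error of 5%, the sample size needed is 169 participants", from about 300 students and an assumed 50% response.
- n0 = 1.96² × 0.25 / 0.05² ≈ 384.15
- With finite-population correction: 384.15 / (1 + 383.15/300) = 168.7, rounded up to 169
- 169 × 1.15 = 194.35, i.e. 194

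Both figures reproduce. The check below uses n = 169.

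**2. Why least squares can go wrong on a 0/1 response.** The variance at predictor value x is p(x)(1 − p(x)), which is not constant. When the disorder is uncommon and risk rises with x, the variance is largest at high x, where leverage is also high, so the model-based standard error is too small. Near 50% prevalence the variance is largest in the middle, and the standard error is too large.

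Worked case, prevalence 10% and odds ratio 2 per SD: the population least-squares slope is ln(2) × E[p(1 − p)] ≈ 0.693 × 0.086 ≈ 0.060. The fitted line 0.10 + 0.060x crosses zero at x ≈ −1.68, and about 4.7% of a normal predictor lies below that. Sampling variation in the slope raises this to about 6%.

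**3. Simulation.** Inputs assumed, not in the article: prevalence 5% to 50%; one standard-normal podiatric predictor; odds ratio 2 to 2.5 per SD; outcomes drawn from a logistic model; ordinary least squares with model-based t intervals. Coverage is for the population least-squares slope.

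| Prevalence | Coverage of 95% slope interval | Students with negative fitted risk |
|---|---|---|
| 5% | about 87% to 90% | 8% to 12% |
| 10% | 91% to 93% | 6% to 10% |
| 20% | about 94% | up to 6.5% |
| 30% | 96% to 97% | up to 3.8% |
| 50% | 96% to 97% | under 1% |

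With no association, coverage is about 95% at every prevalence.

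**4. Sensitivity (odds ratio 2).**
- Three normal predictors, prevalence 5%, 10%, 20%, 30%, 50%: slope coverage 89.5%, 92.3%, 94.9%, 96.4%, 96.6%; negative fits 11.2%, 7.7%, 4.2%, 2.2%, 0.3%.
- Eight normal predictors, same prevalences: negative fits 18.4%, 11.9%, 6.5%, 3.5%, 0.5%.
- Three predictors, skewed: slope coverage 70.4% at 5% prevalence, 83.5% at 10%, 93.4% at 30%.
- Heteroscedasticity-robust intervals, one predictor, 5% prevalence: still only about 91%. With 169 × 0.05 ≈ 8 events, sparse data are the larger part of the problem there.

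**The case against.** The strongest reply is that the Statistical Analysis section never says which side of the regression is the response. The podiatric profile is itself a primary outcome, described as objective and quantitative. If a podiatric measure is the response and a disorder is a 0/1 predictor, linear regression is legitimate and no negative risk can arise. The S-FHAI is also called Likert-type with four dimensions, and Table 2 lists skin, nails, structure and pain, so the foot-health parameters may be dimension scores, for which a linear model is a reasonable choice. How items are recorded does not settle what enters the model, and only the majority are said to be present/absent.

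All of this stands, and it makes the point conditional. It does not remove it: the article reasons at least partly from loading to injury (Table 1, on vertical ground reaction force), no score is defined, and no model is offered for a present/absent response.

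A reader might go further and infer that the planned analysis will yield negative risks and intervals that miss 95%. The documents do not support that. They give neither a dependent variable nor a prevalence; under the same assumptions coverage is near nominal at 20% prevalence and above it at 30% to 50%; and with no association it is about 95%, so the test of no association is roughly valid. Nor does the article plan individual risk prediction.

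It may also be said that the before/after test is a separate sentence. It is, and it adds nothing to the regression argument, but the same scale mismatch applies there.

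**Conclusion.** The point holds in conditional form. The article pairs a largely present/absent outcome with methods for continuous or ordered data and leaves the dependent variable of the regression open. If a present/absent item is the response, the harm is material for uncommon disorders (about 5% to 10%) with a real association: under the one-predictor assumptions, slope coverage is some 2 to 8 percentage points below nominal. More predictors increase the negative fits, and a skewed predictor lowers coverage further. For common disorders negative fits are few and the intervals are slightly conservative.

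These figures rest on assumed prevalences, odds ratios and predictor distributions, none of which the article states. The mismatch between recorded scale and named method does not depend on them. It is worth correcting before analysis, but it does not undermine the study as a whole.

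**What to change.** In the Statistical Analysis section:
1. Name the dependent variable of the regression, and say whether foot health enters as single items or as S-FHAI dimension scores.
2. Where a present/absent item is the outcome, use logistic regression; when both visits enter, use GEE or mixed logistic regression with student as the cluster.
3. For before/after change in such items, report the paired difference in proportions with its 95% confidence interval and McNemar's test.
4. Keep linear regression for S-FHAI dimension scores and for continuous podiatric outcomes.

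The cost is analysis wording only: no extra data and no change in sample size. The downside is that rare items may need exact or penalised fitting, or may have to stay descriptive. At 5% prevalence, with about 8 events, no regression would be precise.
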